### Supplement administration

Daily probiotic capsules contain 1 × 10^9^ colony-forming units (CFU) with two strains of *Lactobacillus rhamnosus* and *Lactobacillus reuteri*, as well as magnesium stearate and lactose as carriers. It also contains 130 mg of starch without bacteria in the placebo compound. We used the suggested dosage from a previous study in the treatment of vulvovaginal candidiasis patients due to the lack of evidence-based approaches regarding the appropriate dosage of this probiotic supplement in subjects with PCOS [43].

### Adherence to the intervention

All subjects will receive telephone calls per week and monthly meetings with a dietitian during the intervention to encourage adherence to the diet. We will send a daily reminder via instant messages that inform them when to stop eating and when they are allowed to eat. Furthermore, periodic meetings (once every 30 days) should be promoted for participants to share their experiences and receive support from physicians. Moreover, all people are given detailed written and oral instructions for each meal plan, and as mentioned, there is no difference between people participating in the fasting diet and the low-calorie diet. Monitoring of food programs is done through the daily interaction of the researcher and the participant in the project through phone conversations. If they do not attend more than two consecutive phone sessions or consume 3 inappropriate meals or fail to follow the diet instructions 3 times a week for more than 2 consecutive weeks is considered non-compliant patients [44, 45]. A 3-day 24-h dietary recall will be taken from the participants every 2 weeks to confirm compliance.

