**Methods:**

We will carry out a randomized clinical trial for 8 weeks. Participants will be randomly assigned (1:1:1) to one of the three groups: (1) a 14:10 early time-restricted feeding (TRF) diet with probiotic supplementation (*n* = 30); (2) a 14:10 early TRF diet with placebo supplementation (*n* = 30); (3) a CR diet (energy-restricted 25% of required calories) with placebo supplementation as a control group (*n* = 30). The primary outcomes will be changes in body weight and insulin resistance. However, glycemic control, lipid profile, metabolic parameters, sex hormone-binding globulin, dehydroepiandrosterone, anti-Mullerian hormone, free androgen index, hirsutism, acne, antioxidant and oxidant status, inflammation, anthropometric measures, mental health, sleep quality, appetite, eating behavior, food craving, and blood pressure are secondary outcomes. All outcomes of this study will be evaluated in pre- and post-intervention.

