### Exclusion criteria

Participants will be excluded if they had an antibiotic intake, allergic reaction to the supplement, getting infected with COVID-19, low adherence of patients to the intervention, or taking any medication affecting weight, appetite, hormonal status, carbohydrate, or lipid metabolism during the study.

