### Sample size calculation

By consideration of a type I error of 5% (*α* = 0.05), a power of 80%, according to the mean weight loss of 2.5 kg (a minimum clinically important difference) as the principal outcome and the standard deviation of 3.87 and 3.04 [59], the sample size was computed to be 25 for each group based on the two-sided t-test. Primary outcomes will be measured as a change from baseline. To compensate for an approximate drop-out rate of 5% during the study period, we elevate the final sample size to 30 subjects in each group. To calculate the required sample size Gigacalculator software was used.$$n=\frac{{\left({z}_{1-\frac{a}{2}}+{z}_{1-\beta }\right)}^{2}\left({{s}_{1}}^{2}+{{s}_{2}}^{2}\right)}{{\Delta }^{2}}$$

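### The missed-phone-session rule for non-compliance is tied to no stated call schedule, and exclusion for low adherence is not reconciled with the intention-to-treat analysis

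*Protocol article*

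**What the plan says.** Adherence to the intervention describes phone contact twice. It opens with "All subjects will receive telephone calls per week and monthly meetings with a dietitian during the intervention", whose stated purpose is encouragement, and gives no number of calls. Further down it says "Monitoring of food programs is done through the daily interaction of the researcher and the participant in the project through phone conversations". The next sentence holds the trigger, "If they do not attend more than two consecutive phone sessions", as one of several alternatives; the others concern inappropriate meals and repeated failure to follow the diet over consecutive weeks. Anyone who meets the rule "is considered non-compliant patients".

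Exclusion criteria, which covers events during the study, lists "low adherence of patients to the intervention" among the reasons for removing a participant. It gives no definition of its own and no reference to the adherence section.

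Three other statements bear on the point. Randomization and blinding says that diet is not blinded. Outcomes says that all outcomes are assessed before and after the intervention. Statistical analysis says that everyone who entered is analysed whether or not they completed 8 weeks, with multiple imputation for missing data.

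**The concern.** A rule that counts consecutive missed sessions has a meaning only once the interval between sessions is known. Here two intervals are on offer and the rule names neither, so two members of staff could apply it in good faith and reach different answers for the same participant.

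This matters because of what may follow. The adherence section is the only place where non-compliance is defined, so it is the natural source for deciding who shows low adherence under Exclusion criteria. That exclusion happens after randomisation, and staff may know whether the participant is on time-restricted feeding or calorie restriction. If excluded participants are not measured at week 8, the primary outcomes are missing for people selected by adherence, possibly in different proportions by arm. The stated analysis would then rest on imputed values for them. The article does not say whether exclusion means leaving the intervention, leaving follow-up, or leaving the analysis, and the last of these would contradict Statistical analysis.

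**Working it through.** **Inputs from the article**

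- Duration: "We will carry out a randomized clinical trial for 8 weeks", that is 8 × 7 = 56 days.
- Group size: "we elevate the final sample size to 30 subjects in each group", with three groups, so 90 in total.
- Trigger: more than two consecutive missed sessions, so a run of at least 3.
- Sessions: 8 if calls are once a week (the natural reading of calls per week, though no number is given), or 56 if the daily contact counts.

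**Elapsed time (no assumption about miss rates)**

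Three consecutive misses span 3 days on the daily reading. On the weekly reading they span 3 weeks, or 3/8 = 37.5% of the intervention.

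**Number flagged (assumptions needed)**

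The article gives no miss rate and no expected number of non-compliant participants, so it has no figure to reproduce. Assume that each call is missed with probability p, independently, and that p is the same for daily and weekly calls. Let f(n) be the probability of at least one run of 3 misses in n calls, and q = 1 − p. Then

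f(0) = f(1) = f(2) = 0, f(3) = p³, and f(n) = f(n−1) + [1 − f(n−4)] × q × p³ for n ≥ 4.

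Worked for 8 weekly calls at p = 0.20, where p³ = 0.008 and q × p³ = 0.0064:

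- f(3) = 0.0080; f(4) = 0.0144; f(5) = 0.0208; f(6) = 0.0272
- f(7) = 0.0272 + (1 − 0.0080) × 0.0064 = 0.0335
- f(8) = 0.0335 + (1 − 0.0144) × 0.0064 = 0.0399

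Continuing to n = 56 gives 0.2988. For the other miss rates, with expected counts of 90 in brackets:

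| Assumed miss rate | 8 weekly calls | 56 daily calls |
|---|---|---|
| 5% | 0.07% (0.1) | 0.64% (0.6) |
| 10% | 0.55% (0.5) | 4.8% (4.3) |
| 15% | 1.8% (1.6) | 14.5% (13.1) |
| 20% | 4.0% (3.6) | 29.9% (26.9) |
| 30% | 12.0% (10.8) | 66.8% (60.1) |

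Per arm of 30, the 20% row is 30 × 0.0399 = 1.2 against 30 × 0.2988 = 9.0. The 5% row is below one participant in the whole trial on either reading.

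**Sensitivity to the equal-rate assumption**

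If weekly calls were missed 20% of the time and daily calls 10%, the table gives 4.0% against 4.8%, and the gap almost closes. The numbers flagged are therefore an illustration. The difference in elapsed time is not.

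**The case against.** The strongest reply is that the two sentences describe two different contacts: support calls linked with the dietitian, and daily monitoring by the researcher. A trial can run both, so a reader who infers that the section contradicts itself on call frequency goes further than the text allows. That stands. What remains is that a session could be either contact.

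The context also leans one way. Attending a session suits a scheduled call better than "daily interaction of the researcher and the participant in the project through phone conversations", and another limb of the same rule runs over more than two consecutive weeks, which parallels weekly sessions. Against this, the daily contact is what the sentence immediately before the trigger describes. The readings may not be equally likely, but the article does not settle the matter.

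A reader might also infer that the rule decides who is excluded and so biases the comparison. The documents do not support that as fact. The link from the non-compliance label to exclusion is inferred, missed calls are only one of several triggers, nothing suggests that the rule is applied differently by arm, and Statistical analysis keeps everyone who entered. The intention-to-treat commitment does soften the consequence. It does not supply week-8 measurements for people who have been excluded, and the article does not clearly say that they are taken. A sentence in Data management and monitoring about outcome data for those who discontinue or deviate may have been meant that way, but as written it speaks of giving them a list.

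Finally, call logistics are detail that an article may leave to the full protocol. That would excuse silence about the schedule. It does not excuse printing a rule that depends on the schedule beside two candidates for it.

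**Conclusion.** The point holds in a limited form. The missed-session trigger is not fixed: it could mean about 3 days or, if calls are weekly, about 3 weeks, and this needs no assumption beyond the weekly reading of a phrase that carries no number. Exclusion for low adherence after randomisation is also left unreconciled with an analysis of everyone who entered.

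How many participants this touches is uncertain. With independent misses at equal rates, the daily reading flags roughly 5.6 to 9 times as many as the weekly reading across miss rates of 5% to 30%. At 5% both counts are negligible, and the gap becomes material from about 10%. Clustered misses, or different miss rates for the two kinds of call, would change these figures, so it would be too strong to say that the two readings flag very different numbers whatever happens.

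Bias is a conditional risk. It arises if flagged participants are excluded and then not measured at week 8, and if that happens in relation to adherence and arm. The article leaves this open but does not show that it will occur. The point deserves correction because the change is cheap and protects the randomised comparison.

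**What to change.** 1. In Adherence to the intervention, reconcile the two descriptions of phone contact. State which contact counts as a session and the elapsed time that the trigger implies, and say that the rule is applied identically in all three arms. The schedule and the threshold are for the trial team to choose.
2. Reconcile Exclusion criteria with Statistical analysis: participants flagged as non-compliant are still measured at week 8 and kept in the intention-to-treat analysis, and the flag serves only to define a per-protocol sensitivity set.
3. Trial status expected recruitment to be almost finished by 23 September 2023, before the article's publication on 25 October 2023. The team should therefore also record which reading was used in practice and report the number flagged by arm.

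The cost is a few sentences. No new variable is needed, since the week-8 assessment is already planned for every participant; the only added effort is bringing flagged participants back for it.

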### Outcomes

#### Primary and secondary outcomes

The primary outcomes in this study will be body weight and insulin resistance. However, fasting blood glucose (FBS) levels, lipid profile, insulin levels, homeostatic model assessment for insulin resistance (HOMA-IR), HOMA for β-cell function (HOMA-β), quantitative insulin sensitivity check index (QUICKI), sex hormone-binding globulin (SHBG), dehydroepiandrosterone (DHEA), AMH, free androgen index (FAI), hirsutism, acne, total antioxidant capacity (TAC), total oxidant status (TOS), C-reactive protein (CRP), body mass index (BMI), mental health, sleep quality, appetite, eating behavior, food craving, energy intake, systolic, and diastolic blood pressure will be known as secondary outcomes. All outcomes of this study will be evaluated in pre-and post-intervention.

#### Measurements and assessments

##### Clinical assessment

General information of patients including age, level of education, occupation, marital status, duration of disease diagnosis, time to sleep and time to wake up (sleep time), alcohol consumption, smoking history, antioxidant supplements, herbal medicines, and history of various diseases was collected through a general questionnaire by interview method at baseline.

##### Anthropometric and blood pressure assessment

Body weight will be measured by fasting, without shoes, with minimal clothing, and using a digital scale (Seca, Hamburg, Germany) with a precision of 100 grams at baseline and 8 weeks during the intervention. The height of people will be measured to the nearest 0.5 cm while standing without shoes. BMI will be calculated using the formula of dividing weight in kilograms by the square of height in square meters. To measure blood pressure, patients were asked to rest for 10 min, then the measurement will be done using a mercury sphygmomanometer (Riester, Germany). The blood pressure of each person will be measured twice with a time interval of 10 min, in a sitting position. The average of these two measurements is considered as the patient's blood pressure.

##### Assessment of physical activity

Twenty-four-hour physical activity recall will be used to assess physical activity. Participants will fully record all their activities during the day in the first, second, fourth, sixth, and eighth weeks of the study. The start time, end time, and intensity of each type of activity are recorded in the table. In total, the duration of all your recorded activities should be about 24 h [46]. Changes in physical activity levels during the study will be considered a confounding factor for statistical analysis.

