### Study interventions

Participants will be randomly assigned (1:1:1) to one of the three groups for 8 weeks: (1) a 14:10 early TRF diet (eating ad libitum only between 8:00 AM and 6:00 PM) with probiotic supplementation; (2) an 14:10 early TRF diet (eating ad libitum only between 8:00 AM and 6:00 PM) with placebo supplementation; (3) a CR diet (energy-restricted 25% of required calories) with placebo supplementation as a control group.

During the TRF period, subjects are instructed to eat freely from 8:00 AM to 6:00 PM daily (for 10 h). While from 6:00 PM to 8:00 AM the next day (14 h), people will only be allowed to drink water, tea, and black coffee without sugar or any calorie-free drink. In addition, individuals will be suggested not to alter the composition of their usual diets throughout the TRF intervention. Furthermore, PCOS patients will be asked to consume a small handful of nuts consisting of 200 kilocalories of mixed nuts (18 g of fat, 5 g of protein, and 4 g of carbohydrates) during fasting if they experience drops in energy or severe headache [40].

In the CR diet of the control group, the daily calories will be calculated by a dietitian. Based on the Harris-Benedict formula, the basal metabolic rate (BMR) of patients will be calculated individually [41]. Then, the total daily energy needed by each person is calculated based on his physical activity and considering the thermogenic effect of food (TEF). Finally, 25% of the required calories [42] will be reduced. Subsequently, this daily caloric requirement will be divided into six-meal menus including 3 main meals and 3 snacks with a macronutrient ratio of 55% carbohydrates, 30% fat, and 15% protein. Based on this, a food menu will be prepared, and the necessary alternatives will be taught to the people of the control group. All participants will also take a probiotic or placebo supplement after breakfast with a glass of water.

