### Randomization and blinding

A stratified permuted block randomization (a fixed block size of *n* = 6) was done using computer generated random numbers by the project coordinator. In this method, eligible patients who meet the study entry criteria are selected and then randomly allocated with stratification by BMI (between 25 and 30 and 30 and 35 kg/m^2^). People will be allocated to one of the three groups, IF diet with a probiotic supplement, IF diet with a placebo, and CR diet with a placebo. Random allocation will be based on a random number list; the letters A, B, and C will be assigned to an equal number of a random number list.

Placebo and probiotic supplements will be produced by TakGen Zist Pharmaceutical Company (Tehran, Iran) and will be placed in the same packages with similar color, flavor, and taste. Then packages will be placed in paper boxes and receive a special code. Placebo and probiotic supplement codes will remain with the company until the end of the study for blind researchers, laboratory staff, outcome assessors, and patients. However, no blinding will do in terms of diet (fasting or CR). In other hand, we do not anticipate any requirement for unblinding but if required, the trial manager, data coordinator, implementation support facilitators, and care home managers will have access to group allocations and any unblinding will be reported.

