### Statistical analysis

All analyses will be performed according to the Intention to Treat Analysis (ITT) method. Therefore, all participants who entered the study (regardless of whether they completed the 8-week study period) are included in the analysis. Missing data will be checked by multiple imputations. Statistical analysis will be conducted using the SPSS software (Version 24, SPSS Inc., and Chicago, IL, USA). The scatter diagram, histogram, and Kolmogorov–Smirnov test will be applied to examine the normality of the data. Normally distributed variables will be reported as the mean and standard deviation, while the median and interquartile range (IQR) will be used for reporting non-normally distributed variables. Moreover, we will use the chi-square test and Fisher’s exact test to compare categorical variables. Also, the independent sample *t*-test and Mann–Whitney U test will be applied to compare continuous variables between-group, whereas we will use paired sample *t*-test and Wilcoxon rank-sum test for within-group comparisons. To compare the differences in primary and secondary outcomes between the two study groups at the end of the trial and adjust the final findings for potential confounders, we will apply the mixed linear effect model. To correct for multiple comparisons and reduce alpha error, *q* values will be used using the Benjamin-Hochberg method. Based on this, significance was defined in *P* values less than 0.05 and *q* values less than 0.1. Cohen’s *d* will be calculated based on the mean and standard deviation. The effect sizes 0.20, 0.50, and 0.80, respectively for low, medium, and high therapeutic effects of the dietary intervention will be determined. No subgroup analyses are planned. However, no interim analyses are planned for this trial.

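### Change in physical activity during the trial is named as a confounder to adjust for, but it arises after randomisation and may be an effect of the diet

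*Protocol article*

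**What the plan says.** Under Assessment of physical activity, participants record their activities "in the first, second, fourth, sixth, and eighth weeks of the study", and the section ends with a rule for the analysis: "Changes in physical activity levels during the study will be considered a confounding factor for statistical analysis".

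The Statistical analysis section states that all analyses follow intention to treat. To compare primary and secondary outcomes between groups and "adjust the final findings for potential confounders, we will apply the mixed linear effect model". It gives no covariate list. It also plans independent-sample t-tests and Mann–Whitney tests between groups, and does not say which analysis is the primary one.

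Other relevant statements are:
- Primary and secondary outcomes: "The primary outcomes in this study will be body weight and insulin resistance".
- Sample size calculation: "Primary outcomes will be measured as a change from baseline".
- Randomization and blinding: patients are "randomly allocated with stratification by BMI", in two strata (25 to 30 and 30 to 35 kg/m²). Diet is not blinded.
- Discussion: time-restricted feeding (TRF) is described as able to act on energy expenditure.

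**The concern.** A confounder is a common cause of treatment and outcome. Treatment here is assigned at random, so nothing that happens afterwards can be a cause of it. Change in activity between weeks 1 and 8 can only be a consequence of the diet, a prognostic variable measured after baseline, or both.

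The article itself makes the first possibility plausible. The Discussion links TRF to energy expenditure, and Study interventions provides for TRF participants whose energy drops while fasting. Because diet is open, behaviour may also change differently by arm.

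If activity lies on the path from diet to weight or insulin resistance, conditioning on it removes that part of the effect. If activity and outcome also share an unmeasured cause, such as motivation, conditioning on activity adds a second, non-causal component. Either way the adjusted contrast is no longer the total effect of being assigned to a diet, which is what an intention-to-treat analysis is meant to estimate. Change in activity is the only variable that the article expressly names as a confounder for the analysis, so an analyst following the text would put it in the model.

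**Working it through.** **Figures in the plan.** The article gives no figure for the effect of diet on activity or of activity on weight, so the bias has to be illustrated on assumed values. From Sample size calculation I take the 2.5 kg difference, the SDs of 3.87 and 3.04, two-sided α of 0.05 and 30 per arm. That section's own 25 per group is not reproduced by its formula: (1.96 + 0.8416)² × (3.87² + 3.04²) / 2.5² = 7.849 × 24.2185 / 6.25 = 30.4, so 31. That is a separate matter and nothing below depends on it.

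**Bias from adjustment.** Let *a* be the between-arm difference in activity change (in SD) and *b* the weight change in kg per SD of activity. Hold the true total effect at −2.5 kg.
- With no shared unmeasured cause, adjusted effect = −2.5 − *ab*.
- As an assumed shared cause, take a standard normal variable that raises activity by 0.5 SD and lowers weight by 1 kg per unit. Then adjusted effect = −2.5 − *ab* + 0.5*a*.

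These were checked by simulation (2,000 trials per setting, 30 per arm, residual SD 3.2 kg):

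| *a* (SD) | *b* (kg per SD) | Formula, no shared cause | Simulated, no shared cause | Simulated, shared cause |
|---|---|---|---|---|
| 0 | −0.5 | −2.50 | −2.50 | −2.51 |
| 0 | −1 | −2.50 | −2.50 | −2.49 |
| 0.25 | 0 | −2.50 | −2.52 | −2.38 |
| 0.25 | −0.5 | −2.375 | −2.35 | −2.25 |
| 0.25 | −1 | −2.25 | −2.26 | −2.16 |
| 0.5 | 0 | −2.50 | −2.49 | −2.24 |
| 0.5 | −0.5 | −2.25 | −2.27 | −1.99 |
| 0.5 | −1 | −2.00 | −1.98 | −1.75 |

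Three things follow.
- When *a* = 0 the adjusted estimate stays at the true value, with or without a shared cause.
- When *a* is 0.25 to 0.5 and *b* is −0.5 to −1, the formula loses 0.125 to 0.50 kg, which is 5% to 20% of 2.5 kg.
- The direction is not fixed. If the diet lowers activity relative to control, *a* is negative and the adjusted effect is overstated: −2.5 − (−0.25)(−0.5) = −2.625 kg, and −2.5 − (−0.5)(−1) = −3.0 kg.

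**What attenuation means for power.** SE of the difference = √(24.2185 / 30) = 0.90 kg. Normal-approximation power is 79.5% at 2.5 kg. If the SE is unchanged by adjustment (assumed), power is about 74% at 2.35 kg and 60% at 1.98 kg.

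**What baseline adjustment would gain.** With equal variances σ² and pre–post correlation *r*, a change score has variance 2σ²(1 − *r*), and the baseline-adjusted value has σ²(1 − *r*²). The ratio is (1 + *r*)/2. All values of *r* are assumed:
- Weight: 0.90 at *r* = 0.80, 0.95 at 0.90, 0.975 at 0.95 and 0.99 at 0.98, a gain of 1% to 10% of variance.
- Insulin resistance: 0.80 at *r* = 0.6, a gain of 20%.

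**The case against.** The strongest defence is that the bias is conditional. It needs the diets to shift activity by different amounts, and the article gives no evidence of how large that shift is. If there is none, adjustment is harmless. This stands, so the statement has to be that the estimate can be biased, not that it is.

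Second, the Statistical analysis section also lists unadjusted between-group tests under intention to treat, so an unadjusted randomised contrast will exist. This stands too: the article does not make the activity-adjusted model the sole primary result. But it uses the adjusted model for the primary outcomes, and it does not say which result takes precedence.

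A reader might infer that the plan leaves the baseline value and the BMI stratum out of the model. The text does not support that. The list of confounders is open, neither variable is excluded, a mixed model on pre and post values can carry baseline as an outcome, and an article may leave the covariate list to the analysis plan. Omitting the stratum would not bias the effect. It costs some precision and tends to make standard errors conservative.

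A reader might also infer a severe loss of power, on the view that week-8 weight will be compared without reference to baseline because the model compares groups at the end of the trial. The Sample size calculation section defines the primary outcomes as change from baseline, so that reading fails.

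**Conclusion.** The point holds in a limited form. The protocol article names a post-randomisation variable as a confounder and attaches confounder adjustment to the model that compares the primary outcomes. That classification is wrong in a randomised comparison, and it conflicts with the stated intention-to-treat aim.

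The consequence is a possible bias, not a demonstrated one. On the assumed values, a true −2.5 kg is estimated as about −2.35 to −1.98 kg, or −2.25 to −1.75 kg if activity and weight also share an unmeasured cause of the assumed strength. It is unbiased if the diets do not differ in their effect on activity, and overstated if the diet under test lowers activity relative to control.

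The case for naming baseline and stratum as model terms is a recommendation, not the correction of a stated error. Its precision gain is modest for weight and larger for insulin resistance only if that outcome's pre–post correlation is lower.

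**What to change.** 1. In Assessment of physical activity, replace the closing sentence. State that change in activity will be summarised by arm and, if wanted, examined in a labelled exploratory mediation analysis. It should not be a covariate in the primary model.
2. In Statistical analysis, state that the primary model for each primary outcome contains arm, the baseline value of that outcome and the BMI stratum (25 to 30, 30 to 35).

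Substituting baseline activity as a covariate is not offered here, because the article schedules no activity record before randomisation; the first is in week 1.

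The cost is two sentences and no new data: the baseline outcome values and BMI are already collected. The change should be fixed before the outcome data are analysed.
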